### Study Events and Assessments

A schedule of study events and assessments is provided in Figure 1.

**Figure 1 figure1:**
[figure not shown]
Schedule of study events and assessments. Study assessments on the right are conducted at the corresponding study events on the left. BDI: Beck Depression Inventory; CT: computed tomography; FTMTRS: Fahn-Tolosa-Marin Tremor Rating Scale; MDRS: Mattis Dementia Rating Scale; QUEST: Quality of Life in Essential Tremor Questionnaire.

Eligibility criteria.Inclusion criteria:Aged 25 to 80 years, inclusiveEssential tremor according to the criteria of the consensus statement of the Movement Disorder Society [17] with a medical treatment–resistant and disabling postural or intentional tremorStable tremor medication for at least 3 months prior to inclusionAn FTMTRS completed within 42 days prior to surgeryWritten informed consentExclusion criteria:Major depressionDementia (Mattis Dementia Rating Scale [MDRS]≤130)Acute psychosisKnown or persistent abuse of medication, drugs, or alcoholPatient incapabilityNursing care at homeSurgical contraindications or medications that are likely to cause interactions in the opinion of the investigatorPersons who are in a relationship of dependence/employment with the sponsor or the investigatorFertile women not using adequate contraceptive methods or with current or planned pregnancy or nursing period

#### Screening

Screening evaluations must be performed within 42 days prior to neurosurgery. For this evaluation, inclusion and exclusion criteria are checked and validated. The complete pretherapeutic work-up includes a physical examination, medical history, demography, vital signs, body weight and height, tremor-related medications list, quality-of-life questionnaires Short Form (SF)-36 and Quality of Life in Essential Tremor Questionnaire (QUEST) [18], MDRS, Beck Depression Inventory (BDI), FTMTRS [16], and tremor analysis (amplitude, frequency). A preoperative MRI is performed within 4 weeks prior to DBS implantation.

#### Baseline

Baseline visit will be performed on the day prior to neurosurgery and includes assessment of tremor-related medications, FTMTRS, and tremor analysis.

#### Tractography of the Dentatorubrothalamic Tract

As part of the preoperative diagnostic work-up, DTI is performed on a clinical 3 Tesla MRI system (Magnetom Trio, Siemens, Erlangen, Germany) with the following specifications: single-shot, 2-dimensional; spin-echo echo-planar imaging; repetition time (TR), 10,000 ms; echo time (TE), 94 ms; diffusion values, b=0 s/mm^2^and b=1000 s/mm^2^; diffusion directions, 61; slice count, 69; voxel size, 2.0×2.0×2.0 mm^3^; acquisition time, 11:40 min. Deformation correction of the EPI sequence is performed according to Zaitsev et al [19]. DTI tractography applying the fiber assignment by continuous tracking (FACT) algorithm is performed on a StealthViz workstation (Medtronic Navigation, Louisville, KY, USA) with the following parameters: fractional anisotropy level, 0.2; minimal fiber length, 10 mm; seed density, 5.0; maximal fiber cutoff angle, 50°. The seed region of interest (ROI) is placed in the ipsilateral dentate nucleus, while the target region is placed in the ipsilateral precentral gyrus.

#### Day of Neurosurgery

Patients will be randomized within 7 days prior to neurosurgery; the DBS system will be implanted according to the randomized treatment group.

#### Detailed Description of the Deep Brain Stimulation Implantation

After administration of standard antibiotic prophylaxis, a patient in a stereotactic frame (Leksell, Elekta, Stockholm, Sweden) is placed in local anesthesia in group 1 and under general anesthesia in group 2.

A computed tomography (CT) scan is performed, and the image data are transferred to the StealthViz Planning Station (Medtronic, Minneapolis, MN, USA). The previously acquired MRI sequences are coregistered to the stereotactic CT scan, and the trajectories are planned in group 1 (local anesthesia) based on AC-PC coordinates and imaging of thalamic and subthalamic region. The deepest point of the implantation will be the posterior subthalamic region or the caudal zona incerta, respectively, as visualized with a T2-weighted MRI sequence. With this technique a DBS electrode will traverse the Vim region (with the superficial contacts) while reaching the posterior subthalamic region with the most inferior contact. In group 2 (general anesthesia), based on imaging of the DRT, the subthalamic region will also be the inferior-most level of implantation.

In group 1, the bilateral DBS electrode implantation is performed under local anesthesia with the patient in a semisitting position. Using a microtargeting drive (MicroTargeting Star Drive M/E System, FHC Inc, Bowdoin, ME, USA), a test electrode (Cosman Medical, Inc, Burlington, MA, USA) is inserted through a frontal burr hole in the cranium. Macrostimulation is performed to confirm a contralateral clinical benefit (at a low threshold) and to test for side effects (at a high threshold). The definitive DBS electrodes are then implanted under fluoroscopic control. The implantable pulse generator (ACTIVA INS, Medtronic, Minneapolis, MN, USA) in group 1 is then implanted and connected to the DBS electrodes under general anesthesia.

In group 2, the bilateral DBS electrode implantation through a frontal burr hole via the planned trajectories is performed in ongoing general anesthesia under fluoroscopic control and without any further testing followed by the implantation of an implantable pulse generator (ACTIVA INS, Medtronic, Minneapolis, MN, USA), which is then connected to the DBS electrodes.

All patients in group 1 and 2 undergo a postoperative CT scan to corroborate the final DBS electrode localization. The following items will be documented at this visit: duration of surgery (time points of mounting frame, start surgery, stop surgery (= dismounting frame) and serial numbers of implanted components.

#### Follow-Up

At 6 and 12 months after neurosurgery, follow-up visits will be performed. The trial for the individual patient ends at the 12-month visit. On both visits, tremor-related medication, vital signs, quality of life (SF-36, QUEST), FTMTRS, tremor analysis (amplitude, frequency), and BDI will be assessed.

#### Video Assessments

The rating of the FTMTRS will be digitally recorded by video at every visit. The videotapes will be rated during the study period by an external group of movement disorder specialists who are not otherwise involved in the trial. To maintain blinding for the external raters, patients should wear headgear which completely encloses the hair.

### Biostatistical Planning and Analysis

#### Sample Size Calculation

This is a feasibility study in 24 patients with essential tremor (12 DTI tractography-assisted implantations, 12 implantations with conventional intraoperative testing). To obtain estimates for the treatment effect and its variance and, thus, to obtain a solid basis for the sample size calculation of the subsequent confirmative trial, the FTMTRS score at 6 months after intervention and its change from baseline will be subjected to exploratory descriptive analysis. Julious [20] found that a sample size of 12 per group in pilot studies seems reasonable for generation of pilot data. Given a continuous outcome, increasing the sample size beyond 12 per group did not have profound influence on the confidence interval. A dropout rate of 25% is assumed, so 30 patients will be assessed for eligibility.

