**Methods:**

The Deep Brain Stimulation for Tremor Tractographic Versus Traditional (DISTINCT) trial is a single-center investigator-initiated, randomized, controlled, observer-blinded trial. A total of 24 patients with medically refractory essential tremor will be randomized to either DTI tractography-assisted stereotactic surgery targeting the DRT in general anesthesia or stereotactic surgery of the thalamic/subthalamic region as conventionally used. The primary objective is to assess the tremor reduction, obtained by the Fahn-Tolosa-Marin Tremor Rating Scale in the 2 treatment groups. Secondary objectives include (among others) assessing the quality of life, optimal electrode contact positions, and safety of the intervention. The study protocol has been approved by the independent ethics committee of the University of Freiburg.

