### Participants and Recruitment

We plan to recruit 24 male or female patients (12 per treatment group). Patients who are referred to our departments due to disabling medically resistant essential tremor are informed about this study. Patients who give their informed consent are registered in the trial and undergo the screening. Patients who gave their informed consent but do not undergo stereotactic surgery are regarded as screening failures. See Textbox 1 for eligibility criteria.

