#### Randomization

The randomization code will be generated by the clinical trials unit using the following procedure to ensure that treatment assignment is unbiased and concealed from patients and investigator staff. Randomization will be performed in blocks of variable length in a ratio of 1:1. The block lengths will be documented separately and will not be disclosed to the center.

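### The step from 25% dropout to 30 patients assessed does not deliver 12 per group, whether the loss falls before surgery or after randomization

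*Protocol article*

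**What the plan says.** The section Sample Size Calculation sets the size by a rule of thumb. It describes "This is a feasibility study in 24 patients with essential tremor", split 12 and 12, and cites a source for the view that "a sample size of 12 per group in pilot studies seems reasonable for generation of pilot data". The supporting reason is precision: "increasing the sample size beyond 12 per group did not have profound influence on the confidence interval". No effect size, power or significance level enters. The section closes with "A dropout rate of 25% is assumed, so 30 patients will be assessed for eligibility".

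The Methods part of the abstract says "A total of 24 patients with medically refractory essential tremor will be randomized". Participants and Recruitment gives the same total and split, and Randomization specifies a 1:1 ratio. Nowhere is the number randomized raised above 24.

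The article also distinguishes two kinds of loss. Participants and Recruitment says "Patients who gave their informed consent but do not undergo stereotactic surgery are regarded as screening failures". Analysis of Secondary Endpoints lists screening failures and drop-out from the trial as separate rates, both to be evaluated for the confirmatory trial. The primary analysis concerns the Fahn-Tolosa-Marin score at 6 months.

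**The concern.** The sentence presents 30 as a consequence of the 25% rate, so it can be checked. Two things look wrong. First, 30 is what results from adding 25% to 24, and that is not the number from which losing 25% leaves 24. Second, the rate is called dropout, which usually means loss after entry to the trial, yet the allowance is made at eligibility assessment, before randomization. Assessing more candidates cannot replace outcome data lost after 24 have been randomized.

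At stake is how far the design meets its own purpose. The only argument for 12 per group is the precision of the treatment effect and variance estimates that will be used to size the confirmatory trial. That precision depends on how many patients have a 6-month score. Because screening-failure and drop-out rates are also results of this feasibility study, the planning value they will be compared with should refer to one defined loss.

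**Working it through.** **Inputs.** Target 24, 12 per group (abstract; Participants and Recruitment; Sample Size Calculation). Rate 25% and 30 assessed (Sample Size Calculation). Primary time point 6 months (Analysis of the Primary Endpoint).

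**Reproducing the plan's figure.** The article shows no working. Multiplying up gives 24 × (1 + 0.25) = 30, an exact match, so this is probably the formula used; that is an inference. The usual inflation is n/(1 − d) = 24/(1 − 0.25) = 32. Conversely, 30 leaves 24 only if the loss is 1 − 24/30 = 20%.

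**Reading A: the 25% is lost between eligibility assessment and surgery.**
- Expected yield from 30: 30 × 0.75 = 22.5, against a target of 24.
- Number to assess: 24/0.75 = 32, since 32 × 0.75 = 24. The stated figure is short by 2.
- The whole allowance is then used before treatment, so none remains for loss between surgery and 6 months.

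**Reading B: the 25% is lost after randomization.**
- The base is the 24 randomized, not the 30 assessed: 24 × 0.75 = 18, or 9 per group.
- Half-width of the 95% confidence interval for a difference in means, in SD units and without covariates: t(0.975; 2n − 2) × √(2/n).
  - n = 12: t on 22 df × √(2/12) = 0.847.
  - n = 9: t on 16 df × √(2/9) = 0.999.
  - Ratio 0.999/0.847 = 1.18, so about 18% wider.
- Upper 95% confidence limit for the pooled SD as a multiple of its estimate, √(df/χ²(0.025; df)): 1.415 on 22 df and 1.522 on 16 df. Squared, the variance multiples are 2.0 and 2.3.

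These values are for an unadjusted two-group comparison. The planned regression includes the baseline score, so its interval will differ by an amount that depends on the correlation between baseline and 6 months, which the article does not give.

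The two readings are alternatives, and their shortfalls should not be added together.

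**The case against.** The strongest reply is that the only sentence giving the rate ties it to patients assessed for eligibility, and that the section describes the 24 as implantations. On that view 30 candidates are meant to supply 24 operated patients, and dropout is just a loose word for screening failure. The error is then two screened patients. Nothing makes 30 a ceiling on screening, so the trial can still randomize 24. This stands as far as it goes: on Reading A the direct effect is small. It does not rescue the figure, since 25% of 30 still leaves 22.5, and it means that no loss before 6 months is allowed for. Nor is the reading secure, because the article itself lists screening failure and drop-out as separate rates.

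Another reply is that the intention-to-treat analysis retains every randomized patient. It keeps patients in their assigned arm, but it does not supply a missing 6-month score.

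A reader might infer more than the article supports, in three ways:
- That the trial will have only 9 per group at 6 months. This holds only if the 25% is loss after randomization, which the article does not say.
- That 30 patients give 22.5 completers. This treats patients assessed as patients randomized, and no section plans to randomize 30.
- That the plan overstates its precision. It states no half-width, SD limit or power. The intervals will be calculated from the data obtained, so a smaller evaluable number will show as wider intervals, and the effect size for the confirmatory trial is to be a conservative estimate.

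**Conclusion.** The stated figure is wrong as written. A 25% loss, a target of 24 and 30 assessed are not consistent with each other, and on neither reading does the plan's own rate deliver its stated size.

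On Reading A the screening figure is 2 short (30 against 32), and no allowance for later loss is stated. On Reading B about 18 patients would be evaluable at 6 months, and the unadjusted half-width for the difference would be about 1.00 SD instead of 0.85 SD. The article does not settle which reading is meant, so the larger consequence is conditional. Reading B also assumes equal loss in the two arms and that patients who drop out have no 6-month score.

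Severity is minor to moderate. The trial is an exploratory pilot with no power claim, so what is at risk is the width of its intervals and the clarity of its planning assumptions. No confirmatory conclusion is affected.

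**What to change.** Rewrite the last sentence of Sample Size Calculation so that it says which loss the 25% describes.

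- **If it is loss before randomization:** call it screening failure, correct 30 to 32, and add a separate assumption for dropout after randomization with the evaluable number expected at 6 months.
- **If it is loss after randomization:** state that 24 are randomized and about 18 (9 per group) are expected to be evaluable at 6 months. Give the corresponding precision, about 1.00 SD for the unadjusted half-width, or the value for the baseline-adjusted model under a stated correlation. The number to assess for eligibility then needs its own screening-failure assumption.

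The definition of screening failure ends at surgery, while randomization takes place up to 7 days earlier. The revised sentence should therefore say how a patient randomized but not operated on is counted.

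The cost is one rewritten paragraph and either two more patients screened or a less favourable expected evaluable number. The number randomized, the endpoint and the analysis do not change.

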#### Randomization

The randomization code will be generated by the clinical trials unit using the following procedure to ensure that treatment assignment is unbiased and concealed from patients and investigator staff. Randomization will be performed in blocks of variable length in a ratio of 1:1. The block lengths will be documented separately and will not be disclosed to the center.

#### Analysis of the Primary Endpoint

The primary efficacy analysis of this clinical trial will be conducted according to the intention-to-treat principle (ITT). This means that the patients will be analyzed in the treatment arms to which they were randomized, irrespective of whether they refused or discontinued the treatment or whether other protocol violations are revealed. Confidence intervals (95%) will be calculated for means and standard deviations within groups as well as for the difference between groups in the ITT population. The effects of DTI tractography-assisted versus conventional intraoperative testing with respect to the FTMTRS score at 6 months will be estimated and tested within a linear regression model including treatment and the baseline FTMTRS score as covariates. A conservative estimate of the effect size anticipated for a subsequent confirmative trial will be derived from these analyses by a combination of clinical and statistical judgement.

#### Analysis of Secondary Endpoints

Effective tremor reduction (FTMTRS score reduction by 50% is regarded as “response”) at 12 months after intervention will be analyzed in an exact logistic regression model. Tremor reduction measured by tremor analysis and calculation of total power before and 6 and 12 months after intervention will be analyzed the same way as the primary endpoint.

Quality of life will be measured with the SF-36. The 8 summary scales per measurement will be evaluated based on the method implemented in the software program (SAS version 9.2 or higher, SAS Institute Inc) provided along with the questionnaire. Change from baseline will be evaluated for all summary scales after 6 and 12 months as the primary endpoint. BDI, effective contact position (with respect to DRT and AC-PC coordinates) and the volume of activated tissue will be analyzed similar to the primary endpoint using linear regression.

Rates of recruitment per month, screening failures, and drop-out from the trial will be evaluated and considered for the confirmative trial. All secondary analyses will be exploratory.

Safety analyses will be performed for all patients for whom 1 of the treatments was started. Patients will be analyzed according to treatment received. Rates of adverse events and serious adverse events will be calculated with corresponding 2-sided 95% confidence intervals.

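### The only analysis the article names for the 12-month FTMTRS is a 50% responder split in an exact model; the 6-month baseline-adjusted regression, applied to the same data, would be more precise at no cost

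*Protocol article*

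**What the plan says.** The Follow-Up section of the protocol article schedules visits at 6 and 12 months and states that at both "FTMTRS, tremor analysis (amplitude, frequency), and BDI will be assessed". The continuous FTMTRS model appears in Analysis of the Primary Endpoint: the treatment effect "with respect to the FTMTRS score at 6 months will be estimated and tested within a linear regression model", with treatment and baseline score as covariates. Sample Size Calculation also ties the descriptive analysis for planning the confirmatory trial to the 6-month score and its change from baseline.

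For 12 months, Analysis of Secondary Endpoints names one FTMTRS analysis. A 50% reduction counts as response, and response "at 12 months after intervention will be analyzed in an exact logistic regression model". Covariates of that model are not named. The same section sends total power from the tremor analysis (6 and 12 months) and SF-36 change (6 and 12 months) to the primary-endpoint method, and BDI to linear regression. It labels all secondary analyses exploratory.

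**The concern.** The article extends its continuous method to 12 months for other outcomes but not for its main scale. Cutting a continuous score at 50% reduction discards information, and an exact test on 12 per arm is conservative on top of that.

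The trial is meant to supply estimates of effect and variance. A responder model supplies an odds ratio, not a mean difference or an SD. If every patient in one arm responds, which can happen with 12 patients, the conditional maximum-likelihood odds ratio is infinite and its exact interval is unbounded on one side.

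The trial also hopes to show that the two procedures are equal. A test that rarely rejects will usually be non-significant, and that is easily misread as support for equality. A difference with its interval guards against this.

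**Working it through.** **The plan's own figures.** The article states no power for this or any other analysis. The 12 per group is a pilot rule ("a sample size of 12 per group in pilot studies seems reasonable for generation of pilot data"). The only derived number is 30 assessed for eligibility, which is 24 × 1.25 = 30; it does not bear on this point.

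**Inputs from the article.** 12 per arm, 1:1 allocation, response defined as a 50% reduction, exact logistic regression at 12 months. No test level is stated; two-sided 0.05 is assumed, in line with the planned 95% intervals.

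**Assumptions, because the article gives none.**
- True standardized difference d = 1 (range 0.5 to 1.5).
- Normal outcome, with response being that outcome cut at a threshold.
- Reference response rate p₁ of 50-80%.
- Baseline correlation ρ = 0.5 for the adjusted model.
- Treatment as the only term in the exact model, which is then Fisher's exact test.

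**Continuous analysis, n = 12 per arm.**
- t-test: noncentrality d√(n/2) = 1 × √6 = 2.449 on 22 df, critical value 2.074; power 64.9%.
- Baseline-adjusted regression: noncentrality 2.449/√(1 − 0.25) = 2.828 on 21 df, critical value 2.080; power 76.9%.
- Half-width of the 95% CI for the unadjusted difference: 2.074 × √(2/12) = 0.85 SD. Adjusted: 2.080 × √(0.75 × 2/12) = 0.74 SD.

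**Exact responder test, n = 12 per arm.** The second arm's rate is p₂ = Φ(Φ⁻¹(p₁) ± 1). Power is the sum of the binomial probabilities of all tables with Fisher p ≤ 0.05. Size is the same sum with p₂ = p₁.

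| Reference rate | Power, other arm 1 SD better | Power, other arm 1 SD worse | True size |
|---|---|---|---|
| 50% | 28.4% (p₂ = 84%) | 28.4% (p₂ = 16%) | 2.3% |
| 60% | 22.2% (p₂ = 89%) | 33.5% (p₂ = 23%) | 2.1% |
| 70% | 14.1% (p₂ = 94%) | 35.5% (p₂ = 32%) | 1.7% |
| 80% | 5.0% (p₂ = 97%) | 31.8% (p₂ = 44%) | 1.2% |

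The 5.0% is a ceiling effect: when both rates are near 100% there is little left to separate.

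**What it takes to reach p < 0.05.** 12/12 against 8/12 gives p = 0.093; 12/12 against 7/12 gives p = 0.037.

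**Other effect sizes, 12 per arm.** Here the better arm responds at 50%, 70% or 80%, or the two rates lie symmetrically about 50%.

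| d | t-test | Adjusted (ρ = 0.5) | Exact responder |
|---|---|---|---|
| 0.5 | 22% | 27% | 7-10% |
| 0.8 | 47% | 58% | 19-23% |
| 1.0 | 65% | 77% | 28-36% |
| 1.2 | 80% | 90% | 38-50% |
| 1.5 | 94% | 98% | 53-71% |

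In this second table the split keeps about 30-75% of the t-test's power. If a quarter of each arm were lost (12 × 0.75 = 9), the figures at d = 1 on the same basis are 51%, 63% and 20-24%.

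**The case against.** The strongest reply is that power is the wrong yardstick. The trial is sized for estimation, every secondary analysis is exploratory, and no effect size or test level is planned, so there is no planned power to lose. That stands. The percentages above only show how much information the split gives up; even the continuous analysis reaches just 65% unadjusted at an assumed 1 SD.

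Three stronger readings are tempting, and the article does not support them.
- A reader might infer that a durability comparison has been crippled. Durability is not a listed objective; the tremor objectives that carry a time point refer to 6 months.
- A reader might infer that tremor at 12 months has no continuous analysis. It has one: total power is analyzed at 12 months by the primary-endpoint method. As an instrumental measure, however, it cannot supply an FTMTRS difference or SD.
- A reader might infer that the 12-month score is thrown away, or that planning of the confirmatory trial fails. The score is collected, nothing says it will not be summarized, and the full protocol or analysis plan, not shown here, may add a continuous analysis. The planning estimate is tied to the 6-month score, so a 12-month estimate matters for planning only if the later trial uses that time point.

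It is also fair to say that exact logistic regression suits a binary outcome in so small a sample, and that a 50% response is easy to read clinically. This justifies keeping the response analysis, but not making it the only one named. The article states a specific method for this endpoint, so the point does not rest on silence alone.

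**Conclusion.** The point holds as a matter of analysis choice. The article names a responder split as the sole 12-month analysis of its main scale while applying the continuous method at 12 months to other outcomes. With 12 per arm and an assumed 1 SD difference, exact-test power is about 14-36% for reference response rates of 50-70%, and 5-32% at 80%, where the low end is a ceiling effect. The t-test has 65%, and the adjusted regression 77% at an assumed baseline correlation of 0.5. The true size of the exact test is about 1.2-2.3% at response rates from 80% down to 50%, so part of the loss is conservatism.

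All of these figures rest on assumed effect sizes, response rates and correlation, and on an exact model with treatment only. The direction of the loss is the same across the range examined; its amount is not fixed by the documents. The primary analysis is unaffected.

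**What to change.** In Analysis of Secondary Endpoints, state that the 12-month FTMTRS score will be analyzed with the same linear regression as at 6 months (treatment and baseline score), reporting the difference with its 95% CI and the SDs. Keep 50% response at 12 months as a supportive analysis, reported as counts per arm with exact 95% CIs. If the full protocol or analysis plan already contains the continuous analysis, naming it there is enough.

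The cost is about one sentence. The score is already collected at 12 months, so no visit, assessment or patient is added. Recruitment was open when the article was submitted, so the change could be fixed before analysis.
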